# In-person vs mobile app facilitated life skills education to improve the mental health of internally displaced persons in Nigeria: protocol for the RESETTLE-IDPs cluster randomized hybrid type 2 effectiveness-implementation trial

**DOI:** 10.1186/s12913-024-11762-x

**Published:** 2024-10-22

**Keywords:** Internally displaced persons, Mental health, Life skills education, Armed conflict, Sexual violence, MHealth, WhatsApp, Digital Health, Forced displacement, Nigeria

## Abstract

**Background:**

Internally displaced persons (IDPs) in Nigeria face a high burden of mental health disorders, with limited access to evidence-based, culturally relevant interventions. Life skills education (LSE) is a promising approach to promote mental health and psychosocial well-being in humanitarian settings. This study aims to evaluate the effectiveness and implementation of a culturally adapted LSE program delivered through in-person and mobile platforms among IDPs in Northern Nigeria.

**Methods:**

This cluster-randomized hybrid type 2 effectiveness-implementation trial will be conducted in 20 IDP camps or host communities in Maiduguri, Nigeria. Sites will be randomly assigned to receive a 12-week LSE program delivered either through in-person peer support groups or WhatsApp-facilitated mobile groups. The study will recruit 500 participants aged 13 years and older. Intervention effectiveness outcomes include the primary outcome of change in post-traumatic stress disorder (PTSD) symptoms assessed using the PCL-5 scale, and secondary outcomes of depression, anxiety, well-being, and life skills acquisition. Implementation outcomes will be assessed using the Acceptability of Intervention Measure (AIM), Intervention Appropriateness Measure (IAM), and Feasibility of Intervention Measure (FIM). Both sets of outcomes will be compared between the in-person and mobile delivery groups. Quantitative data will be analyzed using mixed-effects linear regression models, while qualitative data will be examined through reflexive thematic analysis. The study will be guided by the Reach-Effectiveness-Adoption-Implementation-Maintenance (RE-AIM) framework.

**Discussion:**

The RESETTLE-IDPs study addresses key gaps in the evidence base on mental health interventions for conflict-affected populations. It focuses on underserved IDP populations, evaluates the comparative effectiveness of in-person and mobile-delivered LSE, and incorporates implementation science frameworks to assess contextual factors influencing adoption, fidelity, and sustainability. The study employs a community-based participatory approach to enhance cultural relevance, acceptability, and ownership. Findings will inform the development and scale-up of evidence-based, sustainable mental health interventions for IDPs in Nigeria and other humanitarian contexts.

**Trial registration:**

ClinicalTrials.gov, NCT06412679 Registered 15 May 2024.

**Supplementary Information:**

The online version contains supplementary material available at 10.1186/s12913-024-11762-x.

## Background

Nigeria is facing a humanitarian crisis, with over 3.2 million people internally displaced due to armed conflicts, communal violence, and natural or man-made disasters exacerbated by climate change [1, 2]. As the United Nations Office for the Coordination of Humanitarian Affairs (OCHA) explains, “People become internally displaced when they are forced to leave their homes due to conflict, violence, human rights violations, natural hazards, or other crises within the borders of their country. This can include situations where people move voluntarily to seek safety or to access essential services” [3]. The Boko Haram insurgency and farmer-herder clashes have been major drivers of forced displacement in Nigeria, particularly in the northern regions [4]. This mass displacement has led to a surge of internally displaced persons (IDPs) who live within the borders of the country, in overcrowded, under-resourced camps and host communities, where they face numerous challenges to their physical and mental well-being [5–7].

Mental health disorders are alarmingly prevalent among Nigerian IDPs compared to the general population. A recent study found that 75% of IDPs affected by the Boko Haram conflict experienced clinically significant psychological distress [8]. The prevalence of symptoms of post-traumatic stress disorder (PTSD) ranges from 75 to 94% among IDPs, while symptoms of depression and anxiety were experienced by 60–98% and 66–99%, respectively [8–10]. These rates far exceed the national averages of 20–30% for mental health disorders in the general population [11]. The mental health burden is also high among internally displaced children and adolescents, with up to 67% experiencing PTSD and 54% showing symptoms of depression [12–14]. Considering that the onset of most mental illnesses occurs between the ages of 12 and 25 years [15]. Traumatic experiences such as conflicts, famine, and forced displacement can have significant immediate and long-term impacts on these developing minds, including acute stress reactions, PTSD, chronic depression, substance abuse, and difficulties in social and occupational functioning [16]. These experiences during critical developmental stages can shape an individual’s mental health trajectory well into adulthood.

Women and girls in IDP camps are disproportionately impacted by sexual exploitation, trafficking, forced marriage, and other forms of gender-based violence (GBV) [17]. A study in Northeast Nigeria found that over one-third of displaced women experienced sexual violence, while a fifth reported physical violence. However, only a fraction sought care due to the limited availability of GBV services and fear of stigma [17]. Displacement also disrupts access to education, livelihoods, and social support systems, further compounding the risks to mental health and psychosocial well-being.

Despite the immense needs, there is a dearth of evidence-based, culturally-adapted interventions to address the mental health crisis among IDPs in Nigeria and other humanitarian settings. Most existing services focus on short-term relief aid rather than psychosocial supports and resilience-building resources that would enable IDPs sustainably support themselves move towards mental health and well-being [18]. Conventional facility-based mental healthcare is often inaccessible or inadequate to meet the complex needs of IDP populations due to inadequate mental healthcare workforce, with less than 300 psychiatrists for a population of over 200 million [19–21].

Life skills education (LSE) has emerged as a promising approach to promoting mental health and well-being among conflict-affected populations [22–25]. The World Health Organization (WHO) defines life skills as ‘*a set of abilities that enable individuals to effectively handle the challenges and demands of daily life*’ [26]. LSE programs aim to equip individuals with cognitive, behavioural, and interpersonal skills to effectively cope with stressors, navigate challenges, and make healthy decisions [27, 28]. Studies have shown that LSE interventions can significantly reduce symptoms of depression, anxiety, PTSD, and aggression while improving self-esteem, social connectedness, and problem-solving among youth in humanitarian settings. For instance, one study of young adults in Iran found that, following 2 months of LSE, the mean scores of poor general health decreased by 22 (SD = 18.15, t = 11.2), anxiety decreased by 6.17 (SD = 4.2, t = 8.94) (*P* < 0.01,), social function deficit decreased by 4 (SD = 5.5, t = 6.35), and depression decreased by 7.3 (SD = 3, t = 6.6) [29]. Another clinical trial investigating the effectiveness of LSE on the mental health of middle school students found that LSE had a significant effect on four variables of mental health (stress, violence, addiction, sensation-seeking) (Eta-2 = 0.245; *p* < 0.001) [30]. Additionally, a clinical trial demonstrated the effectiveness of LSE in enhancing food resource management ability, health, and food security status among individuals seeking financial aid to avoid homelessness [29]. Another review found small to medium effect sizes for mental health outcomes and large effect sizes for relevant life skills across various adolescent health areas, including mental health. The effect sizes were categorized as small, medium, or large based on the magnitude of the standardized mean difference (SMD) calculated for the outcomes analyzed. Specifically, LSE interventions were effective in reducing symptoms of anger (SMD) = 1.234), improving life skills (SMD = 0.755) and functioning (SMD = 0.491), and decreasing PTSD (SMD = 0.327), depression and anxiety (SMD = 0.305). Positively correlated with the following life skills: interventions that targeted parent-child interactions (β = 0.557, *p* < 0.05), the assessment of interpersonal relations (β = 0.204, *p* < 0.05), and stress management (β = 0.216, *p* < 0.05) [31].

Further, most LSE interventions targeted schools (78%), communities (10%) and refugee camps (8%) and were delivered by facilitators such as teachers and specialist providers, and most were focused on vulnerable groups [31]. This highlights the broad scope and target populations of these interventions, as well as the utilizing on training people for their implementation.

Regarding LSE content, 93.3% of articles endorsed behavioral skills, followed by interpersonal skills (86.7%), and cognitive skills (66.7%). Common delivery strategies were individually (55.6%) or in groups (44.4%). None was found using digital technology [31]. Thus, there is evidence that LSE can help displaced persons develop a sense of purpose, increase their self-esteem, and improve their relationships with others, all of which contribute to better mental wellbeing, resilience building and social re-integration. However, the evidence base for LSE among IDPs in Nigeria is limited, and the comparative effectiveness of different delivery models remains unknown. In addition, mental health and psychosocial support services (MHPSS) in Nigeria are not tailored to the unique needs of IDPs due to the limited involvement of the end-users, affecting the acceptability and successful implementation [32, 33]. Empowering IDPs to attain the highest standard of mental health and wellbeing can be achieved through a community-partnered participatory approach to implementation [34]. A community-partnered participatory approach is a collaborative and structured engagement of service users (community members), providers, and local stakeholders in planning and implementing targeted solutions specific to their needs [35–37]. This approach has improved mental health-related quality of life and service use in under-resourced communities [38, 39].

Digital technologies offer new opportunities to expand access to mental health support for hard-to-reach IDP populations [40–42]. Mobile phones are increasingly available and utilized among displaced communities in Nigeria. A recent study found that WhatsApp was the most used social media platform among IDPs in Borno State [43]. Harnessing mobile platforms like WhatsApp to deliver LSE content and facilitate peer support groups could help overcome barriers of stigma, insecurity, and limited resources that hinder in-person participation. However, the feasibility, acceptability, and effectiveness of Mobile-based LSE compared to in-person formats have not been rigorously evaluated in humanitarian contexts.

To address these gaps, we propose the Rebuilding Emotional Stability and Strength Through Therapeutic and Life-Skills Education for Internally Displaced Persons (RESETTLE-IDPs) study, a cluster-randomized type 2 effectiveness-implementation trial that aims to:

Co-design and implement a culturally adapted LSE intervention curriculum with IDP communities and local stakeholders in Northern Nigeria;Evaluate the effectiveness of a culturally adapted LSE intervention in improving mental health and psychosocial outcomes among IDPs;Compare the implementation outcomes of in-person vs. Mobile (WhatsApp)facilitated delivery models for the LSE intervention.Assess the contextual factors, including social, economic, and cultural factors and mechanisms influencing the adoption, fidelity, and sustainability of the LSE intervention in IDP settings; and.Engage stakeholders to co-design strategies for scaling up and integrating LSE within existing humanitarian services in Nigeria and beyond.

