### Sample size and power analysis

The target sample size of 500 participants (250 per arm) was calculated based on the primary outcome of change in PTSD symptoms, as measured by the PCL-5. The sample size was determined to detect a minimum effect size (Cohen’s d) of 0.4, which represents a clinically meaningful difference in PTSD symptoms between the two intervention arms. This effect size is consistent with previous studies of psychosocial interventions for conflict-affected populations [46]. The power calculation assumed a two-sided significance level of 0.05, a power of 80%, and an intra cluster correlation coefficient (ICC) of 0.05 to account for the clustering of participants within IDP camps or communities. The ICC was estimated based on previous cluster-randomized trials of mental health interventions in humanitarian settings [47]. To account for potential attrition, the sample size was inflated by 15%, based on an anticipated dropout rate of 10–15% over the 12-week intervention period. This attrition rate is consistent with previous longitudinal studies of IDPs and takes into consideration the potential challenges of retention in the context of ongoing displacement and insecurity [48].

Based on these parameters, a total of 20 clusters (10 per arm) with an average of 25 participants per cluster (500 participants in total) will provide sufficient power to detect a clinically meaningful difference in PTSD symptoms between the in-person and mobile-delivered LSE interventions, while accounting for clustering and attrition.

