**Fig. 2 Fig2:**
[figure not shown]
The life skills education scope

In the in-person arm, participants will attend weekly 120-minute peer support group sessions facilitated by trained IDP men and women and supervised by local mental health workers. The groups will be gender- and age-segregated (13–15, 16–19, and 18 + years) to create safe spaces for open discussion and skills practice. Sessions will employ interactive and experiential learning techniques such as role-plays, storytelling, games, and art-based activities to enhance engagement and retention.

In the mobile arm (i.e. WhatsApp), participants will join gender- and age-specific mobile groups moderated by trained facilitators. The groups will receive weekly LSE content and exercises through a combination of messages, voice notes, images, and live audio sessions. Participants will be encouraged to share reflections, ask questions, and provide peer support through the WhatsApp chat. Facilitators will stimulate discussion, offer feedback, and monitor participant safety and engagement.

Both arms will receive the LSE intervention for a duration of 12 weeks, with an average of 10–12 participants per peer support group. Fidelity to the intervention will be assessed through structured observations, attendance records, and facilitator logs [52]. Participants will receive the equivalent of $20 US and be provided with snacks during the intervention. Participants will also have access to referral information for additional mental health and social services as needed.

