**Maintenance**	The extent to which the LSE intervention becomes institutionalized or part of routine humanitarian programming for IDPs over time.	- Continuation of the LSE intervention beyond the study period (camp reports, observations) - Integration of the LSE intervention into existing humanitarian services (organizational policies, budgets) - Sustained effects of the intervention on mental health outcomes at 6 and 12-month follow-up (PCL-5, PHQ-9, GAD-7, WHO-5) - Perceptions of the intervention’s sustainability and scalability (stakeholder interviews)

Clinical outcomes will focus on primarily the intervention effectiveness in in changing PTSD symptoms from baseline to post-intervention (12 weeks), as measured by the Post-Traumatic Stress Disorder Checklist for DSM-5 (PCL-5) [54]. The PCL-5 is a 20-item self-report measure that assesses the presence and severity of PTSD symptoms on a 5-point Likert scale, with higher scores indicating greater symptom severity. The measure has been validated in several cultural contexts and shows good psychometric properties and will be validated to the local Hausa Language [55]. Secondary outcomes include changes in depression symptoms (Patient Health Questionnaire-9), anxiety symptoms (Generalized Anxiety Disorder-7), well-being (WHO-5), and life skills acquisition (locally developed measure) [56–58].

Implementation outcomes will assess the acceptability, appropriateness, fidelity, and feasibility of the intervention. To gain a deeper understanding of these factors, a qualitative process evaluation will be conducted throughout the study. This evaluation will explore factors influencing program delivery, participant experiences, and program outcomes, including barriers and facilitators to implementation. Data will be collected through in-depth interviews with program facilitators, key stakeholders, and participants, as well as focus group discussions and observations. By examining the intervention’s processes, we aim to inform post-project sustainability and scaling plans. Outcomes will be assessed at baseline, three months, and at the follow up periods of six months and 12-month follow-up by trained research assistants.

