### Data analysis

Implementation outcomes will be assessed using the Acceptability of Intervention Measure (AIM), Intervention Appropriateness Measure (IAM), Facilitator Fidelity logs, observation checklist of program implementation and observation of staff training on the life skills curriculum, and Feasibility of Intervention Measure (FIM) [59]. Cost-effectiveness will be calculated by estimating the total program costs and comparing them to the achieved health outcomes.

Qualitative data analysis will employ a reflexive thematic analysis approach using both inductive and deductive coding strategies to identify key themes related to implementation, acceptability, fidelity, and feasibility. Transcripts will be coded iteratively to identify emerging themes and patterns, with constant comparison within and across cases. Memos and matrices will be used to facilitate synthesis and interpretation. Triangulation of qualitative and quantitative findings will be performed to enhance validity and identify convergent and divergent results [60, 61].

Quantitative data analysis will follow an intention-to-treat approach, using mixed-effects linear regression models to assess intervention effects on primary and secondary outcomes. Models will include fixed effects for time, group assignment, and their interaction, and random effects for clusters and participants. Baseline characteristics will be included as covariates to adjust for potential confounding. missing data will be handled using list wise deletion (complete case analysis) or multiple imputation (MI) methods.

Effect sizes will be expressed using Cohen’s (standardized mean differences) with 95% confidence intervals. To account for potential biases from unmeasured confounders, propensity score matching will be employed to adjust the effect size estimates.

intervals. Subgroup analyses will explore differential effects by gender, age, displacement duration, and baseline symptom severity. Sensitivity analyses will be conducted to assess the robustness of the findings to different assumptions and methods.

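### Objective 2 asks whether LSE works, but both randomised arms receive LSE, so the design can only answer whether in-person and WhatsApp delivery differ

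*Protocol article*

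**What the plan says.** **Aims.** The Background lists five aims. The second is to "Evaluate the effectiveness of a culturally adapted LSE intervention in improving mental health and psychosocial outcomes among IDPs". The third compares the two delivery modes, but on implementation outcomes only. None of the five states a comparison of clinical outcomes between the modes.

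**Study design.** This section says the hybrid design evaluates the clinical effectiveness of LSE, and then adds that it will also permit a comparison of the two arms. Effectiveness of LSE and the comparison of arms are thus presented as two separate products.

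**Table 1.** The Effectiveness row is defined as the impact of LSE on mental health outcomes. The Maintenance row includes "Sustained effects of the intervention on mental health outcomes at 6 and 12-month follow-up".

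**Arms.** The abstract states: "Sites will be randomly assigned to receive a 12-week LSE program delivered either through in-person peer support groups or WhatsApp-facilitated mobile groups". The intervention section confirms: "Both arms will receive the LSE intervention for a duration of 12 weeks". No untreated, waitlist, usual-care or external comparison group is mentioned in the text.

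**Sample size, primary outcome and model.** The effect size of 0.4 is described as a "clinically meaningful difference in PTSD symptoms between the two intervention arms". The primary outcome concerns "changing PTSD symptoms from baseline to post-intervention (12 weeks"). The Data analysis section says: "Models will include fixed effects for time, group assignment, and their interaction, and random effects for clusters and participants".

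**Costs.** "Cost-effectiveness will be calculated by estimating the total program costs and comparing them to the achieved health outcomes". No comparator is named.

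**Limitations.** The Discussion lists self-report, contamination between arms and the difficulty of long-term follow-up and sustainability. It does not list the absence of a group without LSE.

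**The concern.** An aim about whether LSE improves mental health needs a contrast between LSE and no LSE. Randomisation here supplies a different contrast: LSE in person against LSE by WhatsApp. What remains for the stated aim is the change from baseline within the arms. That change mixes any effect of LSE with natural recovery, shifts in security and relief aid, the $20 payment and snacks, access to referral information, and repeated questioning at baseline, 3, 6 and 12 months.

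At stake is what the trial may conclude. The fifth aim and the Discussion look ahead to scale-up. If the arms do not differ and scores fall in both, the aim as worded invites the reading that LSE worked. The same data would arise if LSE did nothing and symptoms eased over time.

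**Working it through.** **1. Which contrast was the trial sized for?** Inputs from Sample size and power analysis: d = 0.4, two-sided alpha 0.05, power 80%, ICC 0.05, 20 clusters of 25, 15% inflation for attrition.

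- Individually randomised: n per arm = 2(1.96 + 0.842)²/0.4² = 98.1, rounded up to 99.
- Design effect: 1 + (25 − 1) × 0.05 = 2.2. Then 99 × 2.2 = 217.8, rounded up to 218 per arm.
- Attrition: 218 × 1.15 gives 251 per arm (502 in total); 218/0.85 gives 257 per arm (514 in total).

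Both are within 3% of the stated 250 per arm and 500 in total. The plan's figure is reproduced, and it is the sample size for in-person against WhatsApp LSE.

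**2. What does each model term estimate?**

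| Term | What it estimates | Randomised? |
|---|---|---|
| Time × group | Difference in change between delivery modes | Yes |
| Group | Difference between modes at the reference time | Yes, but it is about mode |
| Time | Change from baseline under LSE | No; there is no comparator |

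No term estimates LSE against no LSE.

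**3. Can the randomised test separate 'both work' from 'neither works'?** Write the effects of LSE in the two arms as a and b. The contrast is a − b.

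- LSE works equally well in both: a = b > 0, contrast 0.
- LSE works in neither: a = b = 0, contrast 0.

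The test rejects at about 5% in both cases. A larger sample does not change this.

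**4. Is a null between-arm result plausible?** After 15% attrition there are 25 × 0.85 = 21.25 per cluster. The design effect is 1 + 20.25 × 0.05 = 2.0125, and the effective n per arm is 212.5/2.0125 = 105.6. With a normal approximation, power is 83% at d = 0.4 and 66% at d = 0.327. The second value is the PTSD effect that the Background cites from a review of LSE. Even if one mode achieved that whole effect and the other none, the difference would be smaller than the design difference. A null result with falling scores in both arms is therefore a realistic outcome.

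**5. Illustration of how little uncontrolled change would be significant.** The protocol specifies no pooled before-after test, and it does not say whether its ICC refers to change scores. Both are assumptions here.

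- Retained: 500 × 0.85 = 425.
- SE of the mean change = √(2.0125/425) = 0.0688 SD of change.
- Smallest observed change reaching significance: t(19, 0.975) × SE = 2.093 × 0.0688 = 0.144 SD.
- ICC 0.01: design effect 1.2025, threshold 2.093 × √(1.2025/425) = 0.111 SD.
- ICC 0.10: design effect 3.025, threshold 2.093 × √(3.025/425) = 0.177 SD.

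These are thresholds for an observed change. A true change of 0.144 SD would be significant only about half the time. They are not estimates of bias.

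**The case against.** The strongest reply is that the comparative question already drives the trial. The abstract says both sets of outcomes will be compared between the delivery groups. The abstract's discussion and the main Discussion name comparative effectiveness as a contribution, the sample size is for the difference between arms, and the model contains the interaction. On this view the second aim is loosely worded and the trial itself is sound. Much of this stands: the randomised comparison is valid, and the fix brings the aims into line with text already there. It does not dispose of the point, because the Study design section treats the effectiveness of LSE as something distinct from the arm comparison, and the powered clinical contrast is absent from all five aims.

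Four stronger readings are tempting and are not supported.

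- **That the article says the trial will establish that LSE is effective.** No such sentence exists. The Discussion speaks of aiming to generate evidence and of findings that can or will inform scale-up.
- **That the trial will report falling scores as proof of effectiveness.** No pooled before-after test or success criterion based on within-arm change is specified. This is a risk created by the wording of the aim.
- **That the cost-effectiveness analysis is necessarily uncontrolled.** The single condensed sentence names no comparator, but it does not rule out an incremental comparison between arms.
- **That any background improvement of 0.14 SD would be significant.** That figure is a threshold for an observed change under assumed inputs.

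Regression to the mean may also be modest overall, since eligibility sets no minimum PCL-5 score.

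A fuller analysis plan could not rescue the aim as worded. Propensity score matching, which the Data analysis section mentions, cannot create a comparator when every participant receives LSE.

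**Conclusion.** The point holds as a mismatch between a stated main aim and the design. The second aim, the matching sentence under Study design and two rows of Table 1 concern the effect of LSE itself, whereas allocation, sample size and model address delivery mode only. The randomised contrast is zero whether LSE works equally in both arms or in neither, and the remaining evidence is uncontrolled change.

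This conclusion rests on the text describing two arms, both with LSE. The flow diagram is not shown, but the abstract, the sample size section and the intervention section agree. It does not depend on the illustrative threshold of about 0.14 SD (0.11 to 0.18 for ICC 0.01 to 0.10). The comparison of in-person with WhatsApp delivery is unaffected.

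**What to change.** - **Second aim and Study design:** restate both as the comparative effectiveness of in-person versus WhatsApp LSE on PCL-5 change from baseline to 12 weeks, in line with the abstract, the sample size section and the Discussion.
- **Table 1:** in the Effectiveness and Maintenance rows, label within-arm changes at 3, 6 and 12 months as uncontrolled and descriptive.
- **Cost-effectiveness:** state it as the incremental cost and incremental outcome of one delivery mode over the other, with costs recorded by arm.
- **Limitations:** add that there is no comparator without LSE, so improvement common to both arms cannot be attributed to LSE.

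These are changes of wording, apart from the need to keep costs separable by arm. No arm, participant or assessment is added, and the randomisation, primary outcome, sample size and model stay as they are. The price is a more modest headline claim. If the effect of LSE itself must be answered, a concurrent group without LSE would be needed, which is a different and larger trial.
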